Different experimental studies in animal models of DC have shown improvements in ejection fraction and decreases in the ventricular volumes after cell therapy [12–21]. These benefits have also been established in clinical studies aimed at analysing the safety and efficacy of bone marrow-derived progenitor cells in patients with DC [22–31]. In 2006, the ABCD trial [26] described for the first time in humans improvements in the NYHA functional class, a decrease in end-diastolic volume and an average improvement of 5.4% in the ejection fraction in 24 patients with DC treated with intracoronary BM-derived cells. A long term follow-up of this trial showed that the functional benefits achieved were maintained without late adverse effects [25]. Similarly, Fischer-Rasokat et al. [23] observed in 33 patients with DC that intracoronary administration of BM-derived cells appears to be associated with improvements in cardiac contractile and microvascular function in patients with DC (ref). More recently, these results have been confirmed by the REGENERATE-DCM clinical trial [30], in which a 5.37% increase in left ventricular ejection fraction (LVEF) was observed at 3 months after treatment with autologous BM-derived cells combined with peripheral granulocyte colony-stimulating factor (G-CSF). Next to these previous experiences, our group has completed a one-year Phase II Clinical Trial (NCT00629096, EudraCT 2007–003088-36) to evaluate the safety and efficacy of intracoronary infusion of autologous BMMNCs in 27 patients with DC [32]. In this study, an improvement in the New York Heart Association (NYHA) functional class and a reduction of brain natriuretic peptide (BNP) plasma levels were observed without any adverse effect. In addition, a significant decrease in ventricular volumes along with a mean increase in the ejection fraction of 9% in 20 out of the 27 patients was observed at month 6. These changes suggest a favourable effect of cell therapy on ventricular remodelling, which may explain the decrease (or even disappearance) of the degree of mitral regurgitation observed in some patients. However, the gain in ejection fraction after cell therapy varied greatly between patients, ranging from − 9% to + 34%, being this gain greater in patients with a baseline ejection fraction < 25%. The clinical benefit of cell therapy was stable 5 years after infusion, with 69% survival rate and 43% of patients free of major events, staying within a NYHA functional class of I-II [33]. Interestingly, younger patients seemed to show the highest long term response to cell-based therapy in terms of LVEF improvement. However, contradictory reports have been published which show no improvements in ejection fraction, NYHA functional class, or exercise test outcomes after intracoronary infusion of autologous BMMNCs in patients with DC [29]. However these findings should be interpreted with caution as, despite apparent similarities, important methodological differences exist among published reports: BMMNCs dose, LVEF measuring technique, administration procedure, clinical description of eligible patients, subject follow-up length, use of G-CSF, technique of bone marrow cell harvesting etc. Ultimately, clinical studies using BM-derived cells in DC patients have shown only modest benefits [34–36]. We believe that the proposed clinical study may contribute with a new methodological perspective on search for cell therapy-based treatment alternatives in patients with DC. In summary, there is sufficient preliminary evidence to consider intracoronary injection of BMMNCs as a viable, safe and beneficial treatment in patients with DC. However, there is a need for larger, randomized, controlled studies to understand the biological mechanism of action of BMMNCs in the myocardium and the factors affecting clinical response to regenerative therapy with autologous BMMNCs in patients with DC.

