### Angiographic measurement of ventricular function

Angiographic changes in global LVEF at 6 months after cell infusion is the primary endpoint of the trial. Cardiac catheterization is performed to measure systemic and left ventricular end-diastolic pressure, left ventricular function, and coronary flow reserve for each coronary artery as previously published [32]. The left ventricular function studies are based on the analysis of at least one left ventricular angiogram at a 30° right anterior oblique projection. For each ventriculogram measurements, a sinus beat and a post-extrasystolic beat are obtained for the establishment of the contractile reserve of the ventricle. An expert angiographer, blind to treatment allocation and patient progression, will draw the end-diastolic and end-systolic silhouettes using the CASS system. The left ventricular volumes and LVEF are determined and the regional wall motility is analysed. Sheehan’s method [38] is used to study asynergy, dividing the superimposed silhouettes by 100 radii of systolic wall shortening, from end-diastole to end-systole. The abnormal contracting segment is defined as the percentage of radii showing akinesia or dyskinesia. The mitral valve function is evaluated and, when present, mitral insufficiency is graded according to severity.

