### Sample size calculation

A sample size calculation was performed based on the clinical trial study already completed by our group [32]. In this study, a mean increase in ejection fraction of 9.4 ± 9.9% was observed. At the end of the follow-up, mean values of LVEF were 38% among responders, and 27% among non-responders. The sample size calculation was done using GRANMO (v7.12) for paired or repeated measures in two groups. Accepting an alpha risk of 0.05 and a beta risk of 0.2 in a two-sided contrast, 17 subjects are required in the first group and 34 in the second one to detect a difference equal to or greater than 9 units. It is assumed a common standard deviation of 10 and a correlation coefficient between the initial and final measurement of 0.5. A loss to follow-up rate of 10% has been estimated. However, an interim analysis has been planned in order to re-calculate trial sample size based on the mean increase in ejection fraction observed in the first 20 patients that complete a 6 months’ follow-up period.

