### Data management and statistical analysis

Clinical data is manually registered using a paper Case Report Form (CRF). CRF data is entered in the study database using an Electronic Data Capture (EDC) system. After double data entry, resolution of all inconsistencies, and coding by means of medical dictionaries, a final quality control process will be applied. In case of compliance, the database will be considered error free and will be frozen for the statistical analysis of the data. Sponsor and investigator will have access to the final trial dataset.

A descriptive analysis will be performed including all demographic variables collected, as well as baseline clinical data. Qualitative variables will be summarized using absolute frequencies and percentages, while quantitative variables will be described using the mean, median, standard deviation, maximum, minimum and number of observations.

The efficacy evaluation of quantitative parameters will be performed by comparing basal values (prior to the administration of the product) with those recorded in the follow-up visits, using the paired Student’s t-test (if the variable meets the normality requirements), or the Wilcoxon paired test for all other cases. For qualitative parameters, the Chi-square test will be used.

Two interim analyses will be performed during the study. The first one, to ensure the statistical power of the study, will be performed when the first 20 patients reach a minimum follow-up of 6 months, and will include a new sample size calculation based on these data. In the second one, the main variable under study will be analysed once 6-months of follow-up have been completed in all patients recruited. If the results are positive, patients randomised to the control group will be treated via compassionate-use basis with their own cryopreserved BMMNCs, as early mentioned. Per-protocol analysis (PPA) will be used for all efficacy assessments. All p-values and confidence intervals will be calculated and evaluated using a 95% two-sided confidence level.

Safety analysis is aimed at estimating the number and percentage of patients dropped out due to AEs, the number of patients who have experienced at least one AE, the most frequent AEs and the number of patients who experienced at least one SAE. The 95% confidence intervals will be also determined. Safety evaluation will be performed with intention-to-treat analysis.

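### A normality condition chooses the test for the primary LVEF change, and the comparison it names is before-after, although the trial is sized on a mean difference between arms

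*Protocol article*

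**What the plan says.** Under Data management and statistical analysis, the protocol article compares each patient's value before treatment with later values. The sentence begins: "The efficacy evaluation of quantitative parameters will be performed by comparing basal values (prior to the administration of the product) with those recorded in the" (the later visits are meant). A paired t-test is the default, and the condition attached to it reads: "if the variable meets the normality requirements), or the Wilcoxon paired test for all other cases". The article does not say which check decides normality or at what level.

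The primary variable is quantitative, so the rule covers it: "Angiographic changes in global LVEF at 6 months after cell infusion is the primary endpoint of the trial" (Angiographic measurement of ventricular function). No separate primary test is stated.

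The Sample size calculation section works on means in two groups, at a two-sided 5% level with 80% power: "17 subjects are required in the first group and 34 in the second one to detect a difference equal to or greater than 9 units". The variability behind this figure is given as follows: "It is assumed a common standard deviation of 10 and a correlation coefficient between the initial and final measurement of 0.5". Background and rationale reports that in the group's earlier trial "the gain in ejection fraction after cell therapy varied greatly between patients", with extremes of −9% and +34%.

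**The concern.** Two things in this sentence do not fit the rest of the design.

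- **The test is conditional.** A t-test addresses the mean change, which is what the trial is sized on. The signed-rank test addresses the centre of symmetry (pseudo-median) of the changes, which equals the mean only if the changes are symmetric. If skewness triggers the switch, the hypothesis tested changes with it, and the p-value need not agree with a confidence interval for the mean. The two arms may also be given different tests.
- **The comparison is before-after.** The trial is randomised and placebo-controlled, and its size rests on a difference between arms, but the named test compares each patient with their own baseline.

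The 6-month result has consequences: if it is positive at the second interim analysis, control patients are to be offered their own cryopreserved cells. It should be clear beforehand which hypothesis that result answers.

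**Working it through.** **1. The plan's own figure.** Inputs from Sample size calculation: difference 9, SD 10, correlation 0.5, two-sided alpha 0.05, power 0.80, loss 10%; ratio 2:1 from Trial design.

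- SD of change = 10 × √(2 × (1 − 0.5)) = 10.
- Control group n = (1 + 1/2) × (1.96 + 0.842)² × 10² / 9² = 14.5, so 15 controls and 30 treated.
- With 10% loss: 15/0.9 = 16.7, so 17; 30/0.9 = 33.3, so 34. Total 51.

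This reproduces the stated size, and it confirms that the planning quantity is a between-arm difference in mean change.

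**2. Error rate of the rule within one arm.** The documents give neither the normality check nor the shape of the changes, so both are assumed. The check is Shapiro-Wilk at 5%, followed by the one-sample t-test on the change or the signed-rank test, with a true mean change of zero. Skewed shapes are centred gamma distributions. Each cell has 10,000 simulated samples, except skewness 0.7 (4,000). Entries are for n = 30 / n = 34.

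| Shape of change | Check rejects normality | Rule rejects | t-test alone rejects |
|---|---|---|---|
| Normal | 4.6% / 5.3% | 5.1% / 5.1% | 5.0% / 4.9% |
| Symmetric, t with 3 df | 46% / 50% | 5.0% / 4.4% | 4.4% / 4.1% |
| Symmetric, difference of exponentials | 35% / 39% | 5.2% / 4.9% | 4.9% / 5.1% |
| Skewness 0.7 | not tabulated | 6.2% / 6.4% | 5.0% (n = 30) |
| Skewness 1.0 | 44% / 50% | 7.6% / 7.9% | 5.6% / 5.7% |
| Skewness 1.4 | 75% / 81% | 11.0% / 11.1% | 6.4% / 6.0% |
| Mixture, 25% responders | 50% / 56% | 8.1% / 7.6% | 6.1% / 5.3% |

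Monte Carlo error is about ±0.5 points at 10,000 runs and ±0.7 at 4,000. Using the signed-rank test throughout gives almost the same excess (7.8% at skewness 1.0, n = 34). The excess therefore comes from what the Wilcoxon test measures under skew, not from the act of selecting.

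**3. Different tests in the two arms.** At skewness 1.0 the check rejects in 44.4% of samples of 30 and 21.4% of samples of 15. The arms then get different tests with probability 0.444 × 0.786 + 0.556 × 0.214 = 0.47. With normal data, at least one arm switches in 1 − 0.954 × 0.952 = 9% of trials.

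**4. Which skewness is plausible?** The earlier trial gives gains of −9 to +34 (Background and rationale) and 9.4 ± 9.9 (Sample size calculation). Assume both describe the same 27 patients. The extremes are then (−9 − 9.4)/9.9 = −1.86 SD and (34 − 9.4)/9.9 = +2.48 SD. In 20,000 simulated samples of 27, each standardised by its own mean and SD, a minimum at or below −1.86 occurred in 64% (normal), 20% (skewness 0.7), 6.5% (1.0) and 0.6% (1.4). Mild right skew is compatible with the pilot; gamma skewness of 1.4 fits very poorly.

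**5. The same switch between arms.** With identically shaped arms (30 v 15 or 34 v 17) and a t-test or Mann-Whitney choice, the rule rejects in 4.6-5.4% of trials for normal, exponential and lognormal shapes.

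**6. The before-after comparison.** Suppose there is no treatment effect, changes are normal with SD 10, and both arms improve by d points (assumed). The paired t-test in 34 treated patients has noncentrality d × √34 / 10, which is 1.17, 1.75 and 2.92 for d = 2, 3 and 5. It is significant in 20%, 40% and 81% of trials respectively.

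**The case against.** The strongest reply has four parts.

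- **The wording is a routine summary.** A condensed article may leave the normality criterion and sensitivity tests to an analysis plan that is not shown. That holds for the criterion, and its absence is not the point. The article does state a rule, however, and the rule makes the primary test conditional.
- **The switch in itself does little harm.** This stands. For normal and symmetric heavy-tailed changes the error rate stays near 5%, even where the check rejects normality in up to half of samples. A reader might infer that the Wilcoxon test addresses a different hypothesis whenever it is invoked. It does so only if the changes are asymmetric.
- **Large inflation needs strong skew.** This also stands. A reader might infer false-positive rates well above 10%, but the documents give no skewness, a wide spread of gains is not skewness, and the pilot minimum argues against 1.4 or more. Part of any excess also affects the t-test. At skewness 0.7 to 1.0 the net cost of switching is about 1 to 2 points. Nor is the check a coin flip in a placebo arm of 15 to 17: it rejects in 12-14% of samples at skewness 0.7 and 21-26% at 1.0.
- **Between arms the problem almost vanishes.** True for identical shapes. Rates of 7.6% or more appeared only with a skewed treated arm of SD 10 against a normal placebo arm of SD 6, while the plan assumes a common SD. That reply, however, presupposes a between-arm test, which the sentence does not name.

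A reader might also infer that efficacy will be claimed from the treated arm's own change. The Abstract and Trial design say that the arms are to be compared, so the documents do not support that. What they lack is a stated quantitative test that carries out the comparison.

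**Conclusion.** The point holds at moderate size. The only test stated for the primary LVEF change depends on a normality result and is before-after, while the design and its sample size concern a mean difference between arms.

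For the conditional choice, the within-arm false-positive rate on a zero mean change is about 6-8% at 30 to 34 patients if skewness is 0.7 to 1.0 (t-test alone 5-6%). The figure of about 10-11% at skewness 1.4 marks a shape that the pilot does not support. The rate is near 5% without skew, or between identically shaped arms. These figures rest on an assumed Shapiro-Wilk check at 5%, on assumed shapes, and on reading the pilot's range, mean and SD as one set of patients.

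Of the two faults, the before-after comparison is potentially the larger, but its size depends entirely on a shared drift that the documents do not quantify. One change to the text removes both.

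**What to change.** Replace the sentence, for the primary endpoint, with one pre-named between-arm analysis of the 6-month change in angiographic LVEF that estimates a mean difference. An example is a linear model with treatment, baseline LVEF and the age stratum used in randomisation. It should be used whatever a normality check shows. A rank-based test, or a re-randomisation test within age strata, can be kept as a sensitivity analysis that does not replace the primary result.

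The cost is a sentence or two in the analysis section. The sample size of 51 is unaffected: it was derived for a between-arm mean difference, and with the plan's own correlation of 0.5 baseline adjustment would lower the residual SD from 10 to 10 × √(1 − 0.5²) = 8.7. The downside is a small loss of efficiency if the changes are heavy-tailed.

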## Methods and design

### Trial design

The study is designed as randomized, placebo-controlled, double-blind phase IIb clinical trial to compare the functional recovery of patients receiving the conventional treatment for DC in combination with an intracoronary infusion of BMMNCs, using placebo as a control. A 2:1 BMMNC/placebo allocation ratio is used for the randomization of a total of 51 eligible patients. Therefore, a total of 34 subjects will receive BMMNCs infusion, whereas 17 subjects will be treated with a placebo infusion. In order to analyse the predictors of clinical response as well as safety variables, all trial subjects (*n* = 51) are followed for a period of 24 months, completing a total of nine study visits: screening (visit 1), randomization (visit 2), infusion (visit 3), 24 post-infusion (visit 3.1), and months 3 (visit 4), 6 (visit 5), 12 (visit 6), 18 (visit 7) and 24 (visit 8) after the BMMNC/placebo administration (Fig. 1). To allow for sample size re-calculation an interim analysis will be performed with the data from the 6 months post-infusion period of the first 20 patients included. A second interim analysis is planned when the last patient included in the trial has completed study visit 5 (6 months). This early analysis of the data may provide conclusive efficacy (and safety) evidence in order to allow for the authorization of compassionate treatment of finalized patients allocated to placebo. On-completion of protocol standardized 24 months’ follow-up, all patients receiving the experimental treatment will be followed on an observational scheme for an additional period of up to 5 years. This extended follow-up period will provide long term efficacy and safety data of BMMNCs infusion.

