### Study outcomes

The main study variable is the improvement on the ventricular function measured angiographicaly as described below. This efficacy outcome is measured as the changes on the LVEF evaluated by a cardiologist blinded to the patients’ clinical follow-up. With this objective, patients undergo cardiac catheterization in two study timepoints: on the date of the intracoronary infusion of either experimental treatment or placebo (visit 3) and at month 6 (visit 5) after infusion.

Secondary efficacy outcomes include clinical evaluation and NYHA functional grade, BNP or N-terminal fragment of pro-brain natriuretic peptide (NT-proBNP) blood levels, echocardiogram, exercise testing according to Naughton protocol, without oxygen consumption as well as biological parameters of the BMMNC product that may predict a good response (cellularity, chemotaxis and stem cell markers: CD133+, CD34+, CD34+/CD177+,CD34+/CD38-, CD34+/CXCR4+, CD34+/DR-, VEGFR2+, CD90+, CD105+, CD73+, CD14-, CD45-).

Study variables regarding safety are measured as appropriate during follow-up visits: adverse events (AEs) and serious adverse events (SAEs), causally related with study interventions or procedures (including marked changes of vital signs, abnormalities physical examinations and out of range laboratory test results). Additionally, the protocol emphasizes the identification of specific adverse events: major cardiac events or MACEs (defined as cardiac death, major arrhythmia, inclusion in heart transplant waiting list, cardiac resynchronization therapy interventions and hospital admission due to clinically relevant adverse cardiac events), symptoms and signs of arrhythmia, evidence of myocardial harm and tumoral biomarkers abnormalities.

The study design, evaluations and assessment timeline for all variables is illustrated in Fig. 1. After product infusion, all patients are followed-up for 24 months according to protocol by interventional or clinical cardiologists at the participating hospitals. Protocol programmed visits are structured in 9 time-points that include two pre-infusion visits (screening and randomization), BMMNC/placebo infusion day, and 6 post-infusion follow-up evaluation time-points according to a decreasing frequency: 24 h, 3 months, 6 months, 12 months, 18 months and 24 months. Trial investigators must ensure that essential clinical, analytical and exploratory data is registered in the study’s Case Report Form (CRF).

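### The Chi-square rule for qualitative outcomes names no contrast and does not suit NYHA grade: it is too conservative if used between visits and loses power if used between arms

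*Protocol article*

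**What the plan says.** The section on data management and statistical analysis in the protocol article evaluates quantitative efficacy parameters by "comparing basal values (prior to the administration of the product) with those recorded in the follow-up visits". For these it names a paired t-test when the data look normal and a signed-rank test when they do not. The next sentence reads: "For qualitative parameters, the Chi-square test will be used". It gives no exception and no paired, ordinal or exact alternative, and it does not say which groups or time points form the table.

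Under Study outcomes the article states: "Secondary efficacy outcomes include clinical evaluation and NYHA functional grade". Under Trial design, "a total of 34 subjects will receive BMMNCs infusion, whereas 17 subjects will be treated with a placebo infusion". Efficacy is analysed per protocol, so the numbers analysed may be smaller. The article does not expressly call NYHA a qualitative parameter, but no other stated rule clearly covers a graded class.

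**The concern.** The quantitative rule has a fallback for non-normal data; the qualitative rule has none. The sentence follows directly on a before/after comparison, so a reader may apply the Chi-square test to baseline and follow-up NYHA classes. That treats two readings of one patient as two independent patients. If the test instead compares arms, it treats classes I to IV as unordered labels in a table with only 17 placebo patients.

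NYHA improvement was one of the reported findings of the group's own pilot. What is at stake is a real shift in class that the named test would miss more often than a test of equal cost.

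**Working it through.** **1. The plan's own figure.** Inputs from Sample size calculation: "Accepting an alpha risk of 0.05 and a beta risk of 0.2 in a two-sided contrast", "to detect a difference equal to or greater than 9 units", with "a common standard deviation of 10 and a correlation coefficient between the initial and final measurement of 0.5" and 10% loss. The SD of change is 10 × √(2 × (1 − 0.5)) = 10. With 2:1 allocation, the smaller arm needs 1.5 × (10 × (1.96 + 0.84)/9)² = 14.5, rounded to 15, and the larger arm 30. Dividing by 0.9 gives 17 and 34, which matches the plan. This calculation concerns LVEF only; no power is stated for NYHA or any other qualitative outcome. All NYHA distributions, effects and correlations below are therefore assumptions.

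**2. Chi-square between visits.** Let p be the proportion in NYHA III–IV and φ the within-patient correlation of that binary reading. With no change, the difference between visits has variance 2p(1 − p)(1 − φ)/n, but the Chi-square test uses 2p(1 − p)/n. Its true two-sided size is then 2 × [1 − Φ(1.96/√(1 − φ))]. For a latent normal correlation r and p = 0.5, φ = (2/π) × arcsin(r).

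- r = 0.5: φ = 0.33, 1.96/√0.67 = 2.40, size 1.6%.
- r = 0.7: φ = 0.49, 1.96/√0.51 = 2.75, size 0.6%.

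Simulation with 30 patients (34 less about 10%) agrees on size. Power is for NYHA III–IV falling from 40% to 20%:

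| Latent correlation | Chi-square size | Chi-square power | Mid-p McNemar power |
|---|---|---|---|
| 0.5 | 1.6% | 37% | 48% |
| 0.7 | 0.6–0.7% | 35% | 56–57% |

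Mid-p McNemar has size 3.7–3.9% at correlation 0.7. On the full four-class scale with 34 patients and a latent shift of 0.5 SD, the unpaired Chi-square test has power 22% (r = 0.5) or 20% (r = 0.7). Signed-rank has 67% or 83%.

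**3. Chi-square between arms.**

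*Sparseness.* Over four occupied classes the expected placebo count averages 17/4 = 4.25, so at least one is below 5 whatever the distribution. An expected placebo count of 5 needs 5 × 51/17 = 15 patients in that class. Even so, simulated type I error is 3.5–4.8%, close to nominal.

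*Order ignored.* If the effect is a pure trend, 80% power needs noncentrality 7.85 on 1 df and 10.90 on 3 df. The ratio is 10.90/7.85 = 1.39, that is 39% more patients; at a fixed sample size, 80% power falls to 64%. With three occupied classes (2 df) the ratio is 9.63/7.85 = 1.23, and 80% falls to 71%.

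*Simulated power under a proportional-odds shift* (ranges are over repeat runs, or over the three assumed distributions in the last two rows):

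| Placebo v cell arm | Assumed placebo split (%) | Odds ratio | Chi-square | Rank-sum |
|---|---|---|---|---|
| 15 v 30 | 15/45/30/10 | 3 | 30–32% | 43–46% |
| 15 v 30 | 15/45/30/10 | 4 | 47–48% | 61–63% |
| 15 v 30 | 15/50/35, three classes | 3 | 33% | 41–45% |
| 15 v 30 | 15/50/35, three classes | 4 | 51% | 61% |
| 17 v 34 | three four-class splits | 3 | 34–36% | 49% |
| 17 v 34 | three four-class splits | 4 | 54–55% | 68–71% |

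The loss at 15 v 30 is about 8–15 points. At 17 v 34 it reaches 17 points in one split at odds ratio 4.

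**The case against.** The strongest reply is that a journal article names a test family and leaves the variant to the full protocol or SAP. McNemar's test and the linear trend test are themselves chi-square tests, and the before/after contrast is stated only for quantitative parameters. This explains the brevity. But the plain reading is still an ordinary Chi-square test, and the sentence allows no exception, so an SAP that named a rank test would depart from it.

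Other points on that side stand. The pairing fault and the between-arm fault belong to different readings and do not add up. The power figures depend on assumed distributions, and the gap narrows if class IV is nearly empty. It vanishes if NYHA is dichotomised: the uncorrected Chi-square and rank tests then agree, at 57% power for odds ratio 4. The rank test itself misses 37–57% of effects at odds ratios of 3–4 with 15 v 30 and four classes, so the larger part of the problem is sample size.

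A reader might infer from the sparse cells that the between-arm test is invalid. The simulated error rate does not support that. A reader might also take the wrong size of the before/after test to mean spurious positive findings; the error runs the other way.

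**Conclusion.** The point holds as a minor one. The plan fixes a poorly suited test for an ordinal, repeatedly measured secondary outcome and leaves its contrast unstated. Used between visits, the test is far too conservative: its size is about 1–2%, and it loses roughly 11 to 21 points of power against mid-p McNemar at assumed correlations of 0.5–0.7. Used between arms, it keeps its error rate but loses about 8–15 points at odds ratios of 3–4.

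The loss of size under pairing, the 4.25 mean count (with four classes occupied) and the 39% penalty (for a pure trend over four classes) need no assumed NYHA distribution. The simulated power figures do. Nothing here touches the primary LVEF analysis, the total of 51, or the compassionate-use decision, which rests on the main variable.

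**What to change.** Replace the sentence with one that states the contrast and the test for each type of outcome:

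- **NYHA between arms:** Wilcoxon rank-sum on follow-up class, or on change in class, stratified by the age group used at randomisation. The choice between the two should be fixed in advance.
- **Binary outcomes between arms:** an exact or mid-p test.
- **Before/after description within an arm:** Wilcoxon signed-rank for ordinal outcomes, McNemar for binary ones.

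A proportional-odds model adjusted for baseline class can be supportive if the classes are not too sparse. It has not been tested at this sample size and should not be the main analysis on present evidence. The simulations used the unstratified rank-sum test, so the effect of stratifying by age is not quantified here.

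The cost is one sentence of analysis text, with no new data, visits or patients.
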